## Abstract

Mild fasting hypertriglyceridemia is often accompanied by early insulin resistance and atherogenic dyslipidemia, making it an attractive target for pragmatic dietary prevention. This trial aims to determine whether substituting common cereal-based staples with functional low-glycemic index (low-GI) products improves the triglyceride–glucose (TyG) index in adults with fasting triglycerides >150 mg/dL. The GLOW study is an exploratory, randomized, double-blind, single-center crossover trial. Adults aged ≥18 years with fasting triglycerides >150 mg/dL and body mass index ≤30 kg/m^2^ will be enrolled. Participants will follow a stabilized Mediterranean-style diet and will complete two 28-day intervention periods in random sequence: (i) functional low-GI Altograno^®^ pasta, pizza base and flatbread; and (ii) conventional standard wholegrain products. Intervention periods will be separated by a 28-day washout. Study foods will be consumed as fixed daily substitutions of usual staple servings (one bread portion and one pasta or pizza portion). The primary endpoint is the between-intervention difference in TyG response over each period, defined as the period-specific change from the corresponding period baseline to the end-of-period assessment. The primary analysis will compare end-of-period TyG between interventions while adjusting for the period-specific baseline value. Secondary endpoints include fasting triglycerides and glucose, atherogenic lipoproteins (non–high-density lipoprotein cholesterol and apolipoprotein B), inflammation (high-sensitivity C-reactive protein), endothelial reactivity assessed with the Endocheck^®^/Vicorder^®^ system, and food acceptability. Safety endpoints include adverse event recording. Treatment effects will be estimated using linear mixed-effects models accounting for treatment, period and sequence, with prespecified carryover sensitivity analyses. A total of 40 participants will be recruited to generate feasibility data and effect size estimates. This protocol will provide crossover evidence on whether pragmatic, product-level low-GI staple substitution improves TyG and related cardiometabolic and vascular biomarkers in adults with suboptimal triglyceridemia, informing larger trials. Trial registration: ClinicalTrials.gov NCT07198789.

## 1. Introduction

Dietary factors play a major role in shaping the global burden of cardiovascular disease (CVD) and represent a key target for prevention strategies worldwide [1]. In analyses derived from the Global Burden of Disease (GBD) 2019 across 204 countries and territories (1990–2019), approximately 40% of CVD mortality and disability-adjusted life years (DALYs) were attributable to dietary risk factors, with high sodium intake, low whole-grain intake, and low legume intake consistently ranking among the most influential contributors globally [1]. These observations underscore the relevance of dietary strategies focused on improving carbohydrate quality and staple-food choices as pragmatic levers to reduce cardiometabolic risk at scale [1].

In parallel, the increasing prevalence of metabolic disorders has strengthened the need for simple, accessible, and reproducible tools to characterize insulin resistance and cardiometabolic vulnerability in clinical and preventive settings [2]. The triglyceride–glucose (TyG) index, derived from fasting triglycerides (TG) and fasting glucose, has therefore gained attention as a promising surrogate marker of insulin resistance across different stages of the cardiometabolic continuum [2]. Prospective cohort evidence supports its prognostic relevance: in the Vascular Metabolic CUN cohort (VMCUN cohort) (n = 5014; median follow-up 10 years), individuals in the highest TyG quintile exhibited a substantially increased risk of incident CVD compared with those in the lowest quintile (hazard ratio (HR) 2.32, 95% confidence interval (CI) 1.65–3.26), and the addition of TyG to a Framingham-based model modestly improved discrimination (area under the curve (AUC) 0.708 vs. 0.719; *p* = 0.014) [3]. Complementary evidence from the National Health and Nutrition Examination Survey (NHANES) (nine cycles; median follow-up 9.2 years) indicates that TyG may convey mortality information even among participants with normoglycemia, in whom a one-standard-deviation increase in TyG was associated with higher all-cause and cardiovascular mortality (HR 1.35, 95% CI 1.17–1.56; HR 1.38, 95% CI 1.04–1.84) [4]. Beyond cardiovascular outcomes, TyG has also shown clinically relevant performance in metabolic liver dysfunction, with a meta-analysis of 20 studies including 165,725 participants reporting pooled sensitivity 0.73, specificity 0.67, and AUC 0.75 for diagnosing and predicting metabolic dysfunction-associated fatty liver disease/non-alcoholic fatty liver disease (MAFLD/NAFLD) [5].

Dietary carbohydrate quality appears to be a meaningful modulator of glycolipid metabolism and TyG-related profiles, with potential implications for intermediate cardiometabolic risk markers [6]. In PREDIMED-Plus (Prevención con Dieta Mediterránea–Plus) (n = 5373), improvements in a carbohydrate quality index over 6–12 months were associated with concurrent favorable changes across several cardiometabolic traits, including reductions in TG and TyG-related indices [6]. Intervention evidence also indicates that substituting refined cereals with wholegrain cereal-based diets can improve post-prandial metabolic responses, which is mechanistically relevant for triglyceride-rich lipoprotein handling [7]. In a 12-week parallel-group intervention in individuals with metabolic syndrome, a whole-grain cereal-based diet compared with refined cereals significantly reduced post-prandial insulin and TG responses, with average decreases of 29% and 43%, respectively, and significantly lower post-prandial insulin and TG versus controls at study end (*p* = 0.04 and *p* = 0.05) [7]. Observational data further align with this direction, showing inverse associations between whole-grain intake and hypertriglyceridemia, alongside positive associations between refined-grain intake and hypertriglyceridemia and metabolic syndrome [8]. However, evidence from double-blind randomized interventions that test pragmatic, product-level substitution of commonly consumed cereal staples—beyond broad dietary pattern advice—remains limited. In particular, data are scarce on whether functional cereal products formulated to lower the glycemic index can improve the TyG index and complementary vascular function markers in adults with mild fasting hypertriglyceridemia.

To address this gap, we adopted a pragmatic enrichment strategy by enrolling adults with fasting TG > 150 mg/dL, a phenotype in which dietary carbohydrate quality may meaningfully influence insulin resistance-related glycolipid dysregulation captured by TyG [2,6,9]. Accordingly, this double-blind crossover trial will compare functional low-glycemic index pasta, pizza, and flatbread with conventional, commercially available wholegrain counterparts, each consumed as a fixed daily substitution within a stabilized diet, with comprehensive evaluation of TyG and complementary fasting and postprandial glycolipid and cardiometabolic biomarkers.

## 2. Methods

### 2.1. Study Design

This is an exploratory, randomized, double-blind, controlled, single-center crossover trial enrolling healthy adults with suboptimal fasting triglyceride levels. The study aims to compare the effects of a Mediterranean-style dietary pattern enriched with functional low-glycemic index (low-GI) carbohydrate staples versus an otherwise comparable regimen based on conventional wholegrain carbohydrate staples on the TyG index and selected metabolic and vascular biomarkers. Each participant will receive both dietary interventions in a randomized sequence, separated by a pre-specified washout period, enabling within-participant comparisons and improving statistical efficiency by minimizing between-subject variability.

A CONSORT (Consolidated Standards of Reporting Trials)-style flow diagram of participant progression through screening, randomization, crossover periods, washout, and analysis is provided in Figure 1.

### 2.2. Study Setting

The trial will be conducted at the outpatient clinic of the Cardiovascular Medicine Unit, IRCCS Azienda Ospedaliero-Universitaria di Bologna (Policlinico di Sant’Orsola, Bologna, Italy). Biochemical analyses will be performed by trained personnel at the Lipid Laboratory, Department of Medical and Surgical Sciences (DIMEC), Alma Mater Studiorum—University of Bologna.

### 2.3. Eligibility Criteria

Eligibility will be assessed at screening/baseline based on medical history, concomitant therapies, and laboratory findings. Inclusion and exclusion criteria are detailed in Table 1.

The BMI upper limit (≤30 Kg/m^2^) was selected to reduce metabolic heterogeneity and minimize confounding from obesity-related insulin resistance, inflammation, and endothelial dysfunction, thereby enabling a clearer evaluation of the effect of carbohydrate-quality substitution.

### 2.4. Recruitment and Informed Consent

Potential participants will be recruited among adults evaluated at the outpatient clinic. To facilitate enrolment, the study may also be promoted through the sponsoring institution’s official social media channels and, where appropriate, through the Principal Investigator’s professional accounts, in compliance with institutional policies and applicable regulatory requirements. Written informed consent will be obtained prior to the conduct of any study-specific procedures.

### 2.5. Study Products and Administration

Participants will receive two sets of wheat-based cereal staples (pasta and bread-type products), which represent major contributors to habitual carbohydrate intake and are therefore suitable for a pragmatic daily substitution within a Mediterranean-style diet. This product-based substitution strategy was chosen to maximize feasibility, adherence, and generalizability in real-world dietary settings. To preserve blinding, study products will be supplied in neutral, indistinguishable packaging identified only by a study code, with no brand identifiers. The functional intervention comprises Altograno^®^ flour-based pasta, pizza base, and flatbread. These products were selected because their formulation provides higher fiber and protein and lower available carbohydrate than conventional wholegrain products (Table 2), features expected to be associated with a lower glycemic index and attenuated postprandial excursions. The control intervention comprises conventional, commercially available wholegrain pasta, pizza base, and flatbread made from regular wholegrain wheat flour and without additional functional enrichment (e.g., added fibers, resistant starch, or protein concentrates).

Both product sets will be consumed as a fixed daily substitution within a stabilized diet, replacing the usual staple servings typically consumed (one portion of bread and one portion of pasta or pizza per day), without individual dose adjustment. As summarized in Table 2, the product sets are not macronutrient-matched; therefore, the intervention contrast reflects a pragmatic difference in carbohydrate quality and overall nutritional matrix (including fiber, protein, and labeled carbohydrates), rather than glycemic index alone. Study products will be provided free of charge by Casillo SpA (Corato, Bari, Italy).

#### 2.5.1. Nutritional Composition of Study Carbohydrate Products

The nutritional composition of the functional low-glycemic index (low-GI) carbohydrate products (Altograno^®^ pasta, pizza base, and flatbread) and the corresponding conventional wholegrain control products is summarized in Table 2. Values are reported as declared on product labeling; differences in labeled carbohydrates, fiber, and protein reflect the distinct formulations of the functional vs. conventional wholegrain products and are part of the intended product-level substitution.

#### 2.5.2. Product Handling, Storage, and Accountability

Study foods will be delivered to the site prior to screening of the first participant and packaged into predefined kits for each intervention period (28 single-pack pasta portions, 4 pizzas, and 28 flatbread portions). Products will be stored at room temperature (≤25 °C) in a secure area with restricted access, available only to the hospital pharmacist, investigators, or authorized site staff. Products will be managed in accordance with applicable regulatory standards, and treatment logistics will be monitored regularly by the Principal Investigator.

Study products will be pre-numbered, and dispensing will occur only to enrolled participants according to the randomization sequence. The identification number of each dispensed product will be recorded in source documentation and in the electronic case report form (eCRF) using Research Electronic Data Capture (REDCap) to ensure full traceability. Participants will return unused study products and empty or partially used packaging at each visit to support accountability and adherence assessment. Study foods will be used exclusively within the trial.

### 2.6. Randomization, Allocation Concealment, and Blinding

Participants will be randomized in a 1:1 ratio to one of two intervention sequences using computer-generated randomization codes. Randomization codes will be retained in a sealed envelope and accessed only after database lock and completion of the primary data analysis. Study products will be pre-numbered, and dispensing will be documented in source records and in the case report forms.

The study will adopt a double-blind design, with both participants and investigators blinded to treatment allocation. Intervention and control products will be provided in identical packaging and labeled with a study code only. The treatment code will be disclosed only after database lock, unless unblinding is required for safety reasons. Emergency unblinding will be permitted only when deemed essential for clinical management or participant safety and welfare.

### 2.7. Schedule of Assessments

The timing of enrolment, allocation, intervention administration, and study assessments is summarized in Table 3, in accordance with the Standard Protocol Items: Recommendations for Interventional Trials (SPIRIT) guidance. All study parameters will be assessed using standardized methodologies to ensure consistency and reliability of the collected data.

### 2.8. Outcomes

Study outcomes are designed to quantify the comparative effects of functional low-GI foods versus conventional wholegrain foods on glycolipid metabolism and selected vascular biomarkers within a randomized crossover design. Endpoints will be assessed at prespecified trial visits, and analyses will account for treatment, period, and within-participant effects, in accordance with the statistical approach outlined in the protocol.

#### 2.8.1. Primary Endpoint

The primary endpoint is the between-intervention difference in the TyG index response over each 28-day intervention period, defined as the within-participant, period-specific change from the corresponding period baseline (Day 0 for Period 1; Day 56 for Period 2) to the end-of-period assessment (Day 28 and Day 84, respectively). In the primary mixed-effects model, end-of-period TyG will be compared between interventions while adjusting for the corresponding period baseline value, yielding an estimate equivalent to a between-intervention difference in change. The crossover design will enable estimation of within-participant treatment effects while accounting for potential period-related influences.

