### 2.11. Sample Size Determination

This is a pilot study exploring a comparison that has not been previously tested. The SD assumption (0.7 TyG units) was informed by large population datasets reporting a TyG SD of approximately 0.7 in adults. Assuming a two-sided alpha (α) level of 0.05, 80% power, and an estimated standard deviation (SD) of 0.7 units for the primary endpoint, the required sample size is estimated at 33 participants. With the planned enrolment target of 40 participants, the study will be able to detect a between-intervention difference of approximately 0.30–0.35 TyG units (within-participant, period-specific change), which we considered a clinically meaningful effect size for a proof-of-concept trial in this phenotype. To account for potential dropout (approximately 15%) and post hoc exclusions due to non-compliance, the target sample size will be increased to 40 participants. The study is not powered for secondary endpoints, which will be analyzed as exploratory outcomes and interpreted primarily using effect sizes and 95% confidence intervals to inform future trials.

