### 2.12. Statistical Analysis Plan

Analyses will be performed using IBM SPSS Statistics (version 28.0). Continuous variables will be summarized as mean (SD) or median (interquartile range (IQR)), as appropriate, and categorical variables as counts and percentages. Treatment effects will be estimated within the crossover framework using linear mixed-effects models, including treatment, period, and sequence as fixed effects, and participant (nested within sequence) as a random effect to account for within-participant correlation. Accordingly, for the primary endpoint, the treatment effect will be interpreted as the between-intervention difference in period-specific change in TyG. Potential carryover effects will be explored by adding a treatment-by-period interaction term and by comparing period-specific baseline values; if evidence of carryover is observed, sensitivity analyses will be conducted, including analyses restricted to first-period data. Model assumptions (normality of residuals and homoscedasticity) will be assessed; when violated, data transformation and/or non-parametric sensitivity analyses (e.g., Wilcoxon signed-rank test for paired comparisons) will be considered, with paired estimates reported as supportive analyses. A per-protocol analysis will be performed excluding participants with major protocol deviations. Extreme values will be evaluated using the pre-specified approach, including Dixon’s Q test where applicable. All tests will be two-sided, with α = 0.05.

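### The primary TyG model is not reconciled between the Abstract, 2.8.1 and 2.12, and the likeliest reading of its baseline term can lose precision

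*Protocol article*

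**What the plan says.** The Abstract states the primary analysis this way: "The primary analysis will compare end-of-period TyG between interventions while adjusting for the period-specific baseline value". Section 2.8.1 defines the endpoint as change over each period, from Day 0 to Day 28 and from Day 56 to Day 84. It then describes the primary mixed model as end-of-period TyG compared between interventions while "adjusting for the corresponding period baseline value, yielding an estimate equivalent to a between-intervention difference in change".

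Section 2.12 describes linear mixed models "including treatment, period, and sequence as fixed effects, and participant (nested within sequence) as a random effect". The response is not named and no baseline covariate is listed; period baselines appear there only as a carryover check. The next sentence, which is about the primary endpoint, says that "the treatment effect will be interpreted as the between-intervention difference in period-specific change in TyG".

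Section 2.11 gives the planning figures: "Assuming a two-sided alpha (α) level of 0.05, 80% power, and an estimated standard deviation (SD) of 0.7 units for the primary endpoint", with the SD "informed by large population datasets reporting a TyG SD of approximately 0.7 in adults", and a target of "a between-intervention difference of approximately 0.30–0.35 TyG units (within-participant, period-specific change").

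**The concern.** Three estimators can be read from these sections. They differ in the slope b applied to the period baseline:

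- the endpoint definition, taken as an unadjusted change score, fixes b at 1;
- the 2.8.1 and Abstract model estimates b;
- the 2.12 term list, if the response is end-of-period TyG, sets b to 0. If the response is change, it sets b to 1.

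The same data can then give different standard errors and p-values depending on the section followed. The trial is also meant to supply effect-size estimates for larger trials, so an unclear variance would carry forward.

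A second issue depends on how b is estimated. One baseline covariate beside a random participant effect has a single slope, which blends two relations: how participants with higher average baselines differ from others, and how a participant's own baseline shift between periods predicts the end values. Only the second bears on the within-participant treatment contrast. A blended slope that is too steep for that contrast adds baseline noise to it.

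**Working it through.** **The plan's own figure.** Take SD 0.7 as the SD of the within-participant difference, with two-sided alpha 0.05 and 80% power. Then n = (0.7 × (1.960 + 0.842) / 0.35)² = 31.4, so 32 (34 with the t distribution). At 0.34 it is 33.3. The plan says "the required sample size is estimated at 33 participants", so its figure reproduces near the upper end of the stated effect range. This point is not about sample-size arithmetic.

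**Inputs.** σ = 0.7 at each visit (2.11), N = 34, difference 0.35. The article gives no visit correlations, so these are assumed: ρw between baseline and end of the same period, ρb between visits in different periods.

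**Formula.** Let D_E and D_B be the between-period differences in end value and baseline. Then Var(D_E) = Var(D_B) = 2σ²(1 − ρb) and Cov(D_E, D_B) = 2σ²(ρw − ρb). For slope b:

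SE = √{2σ²[(1 − ρb)(1 + b²) − 2b(ρw − ρb)] / N}

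The best slope is the within-participant one, w = (ρw − ρb)/(1 − ρb). The between-participant slope is (ρw + ρb)/(1 + ρb). Relative to w, slope b multiplies the variance by 1 + (b − w)²/(1 − w²).

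**Equal correlation 0.5.** Here w = 0 and the between slope is 1.0/1.5 = 0.67. The single slope fitted by REML averaged 0.43 in simulation.

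- No baseline: √(0.49/34) = 0.120
- Single slope: √(0.49 × (1 + 0.43²)/34) = 0.131
- Change score: √(0.98/34) = 0.170
- Within-participant slope: 0.120 from the formula, 0.122 simulated, because estimating the slope costs one degree of freedom

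Simulated power at a difference of 0.35 was 79–82% with no baseline, 78–80% with the within-participant slope, 73–74% with the single slope and 50–51% with the change score.

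**Other correlations (SE from the formula; fitted single slope from simulation).**

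| ρw / ρb | single slope b | no baseline | change score | single slope | within slope |
|---|---|---|---|---|---|
| 0.75 / 0.75 | 0.71 | 0.085 | 0.120 | 0.104 | 0.085 |
| 0.75 / 0.50 | 0.73 | 0.120 | 0.120 | 0.108 | 0.104 |
| 0.90 / 0.50 | 0.90 | 0.120 | 0.076 | 0.073 | 0.072 |

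**Simulated variance, single slope relative to within-participant slope.**

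- Equal correlation: about 1.04 at 0.3, 1.15–1.19 at 0.5, 1.44–1.48 at 0.75 and 1.66 at 0.85
- AR(1) from 0.5 to 0.85: about 1.06 to 1.17
- Moderately higher within-period correlation (0.6/0.4 to 0.8/0.6): about 1.04 to 1.08
- 0.9/0.5: about 1.00

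Simulated bias was at most 0.005 for every estimator.

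**Link to the planning SD.** Under equal correlation, SD 0.7 for the end-value difference implies ρ = 0.5, since 2(1 − ρ) = 1. SD 0.7 for the change difference implies ρ = 0.75, since 4(1 − ρ) = 1. The power statement therefore also depends on which model is meant.

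**The case against.** The best defence reads the sections together: 2.12 gives a general crossover framework for all endpoints, and 2.8.1 adds the baseline term for the primary one. Nothing in 2.12 excludes a covariate. This is a fair reading, so a reader who infers that the sections are incompatible, or that 2.12 prescribes an end-value analysis without baseline, goes further than the text. But 2.12 goes on to speak about the primary endpoint specifically and draws its interpretation from the listed terms alone. The reconciliation is left to the analyst.

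The claim of equivalence in 2.8.1 can also be defended. With baseline as a covariate, replacing the end value by change shifts the baseline slope by 1 and leaves the treatment coefficient and its standard error unchanged. That holds for a baseline-adjusted change. It does not hold for the unadjusted change by which the endpoint is defined, where the two estimates agree in general only in expectation.

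The single slope is implied, not stated, and such detail may sit in an analysis plan that is not shown. The precision point must therefore stay conditional. A reader might also infer that 2.8.1 always wastes power, or needs some 45% more participants. That size of loss belongs to equal correlation near 0.75. When visits within a period are more alike than visits across periods, the single-slope model beats having no baseline term (0.108 against 0.120 at 0.75/0.50) and comes close to the within-participant slope.

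**Conclusion.** The point holds as an unreconciled specification with a conditional loss of precision. Under randomization and without carryover all readings estimate the same treatment effect, but they are different estimators. At equal correlation 0.5 their standard errors run from 0.12 to 0.17, and power from about 50% to about 80%.

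The single-slope loss against a within-participant slope ranges from nil to about 66% in variance, depending on correlations the article does not give. The within-participant slope was never materially worse than the single slope in any pattern examined.

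A reader might infer that the primary analysis is biased or invalid. The documents do not support that: a baseline-adjusted crossover mixed model is valid, and no bias or Type I error inflation is shown. The matter should be settled before unblinding, but it is not a flaw that undermines the trial.

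**What to change.** State one primary model in the same words in the Abstract, 2.8.1 and 2.12:

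- response: end-of-period TyG;
- fixed effects: treatment, period and sequence;
- random effect: participant;
- baseline: two covariates, the participant's mean of the period baselines and each period's deviation from that mean.

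Regressing the between-period difference in end values on the difference in baselines, with sequence group as the contrast, gives the same treatment contrast among participants who complete both periods. It can serve as a supportive analysis. It should not replace the mixed model, because it drops anyone with one completed period and about 15% dropout is expected.

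In 2.8.1, replace the claim of equivalence with a statement that the coefficient estimates the same target effect, namely the baseline-adjusted between-intervention difference. In 2.11, say which difference the SD of 0.7 refers to.

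The cost is wording and one degree of freedom. If the within-participant baseline carries no information, the standard error is about 2% larger than with no baseline term (0.1225 against 0.1205 in simulation at N = 34).
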